### Implementation of study procedures

Patients who have completed primary treatment (including adjuvant or neoadjuvant chemotherapy, radiation, and surgery) within 12 months and satisfy all the study eligibility criteria are offered study participation by the treating clinician during a standard follow-up visit at a MEDEA participating institution. Signature to study consent is obtained, and patients enter the study. The patient then meets with the study nurse, who collects the required baseline study measures including baseline objective anthropometric measures. Randomization then occurs, and patients are assigned either to the control or to the intervention arm. Patients are then contacted by the study coordinator to go over study material and study intervention schedule if applicable. If a patient is randomized in the intervention arm, they are paired with an individual lifestyle coach, and the study coordinator schedules telephone calls according to the study schema, timeline, and availability of time slots for coaches. The study coordinator oversees the study procedures and assures optimal scheduling and troubleshoots organizational problems. Study materials are sent to patients both in the control and interventional arm, including materials of the Health Education Program and accelerometers for the initial M0 assessment. In addition, patients in the interventional arm receive the participant workbook as a support to the telephone-based sessions. Study procedures then follow the schedule outlined in Table 1 and Fig. 2. The trial is coordinated by Gustave Roussy. A project manager is responsible for all the administrative aspects of the trial, including coordination between centers and between patients and coaches (including scheduling of calls and mailing materials to patients).

### Ancillary and post-trial care

Patients eligible for the MEDEA Study diagnosed with stage I–III breast cancer have completed their primary treatment. After completion of study follow-up (i.e., M18), patients go back to standard-of-care follow-up in the setting of regular surveillance for early-stage breast cancer.

### Data collection, management, and auditing

The Biostatistics and Epidemiology Unit at Gustave Roussy implemented an electronic case report form (eCRF) to allow secure online-direct data collection, using the Trialmaster software suite. Each user has personal identifiers (user ID/password), and data access is strictly limited according to profiles: (1) hospital clinical research assistant (CRA), allowing data entry on the eCRF; (2) data manager, allowing the first data monitoring, perform consistency checks, and edit requests for clarification addressed to the investigator or hospital CRA; and (3) investigator profile, enabled to sign and validate the data electronically. An e-learning is mandatory to access the eCRF. The password is configured when the profile is activated and must be changed every 6 months. For each patient included, the eCRF has to be completed by hospital CRA and signed by a study investigator. An audit trail within the system tracks all the changes made to the data. The data collected through the eCRF are the data source for the analysis. Data collected will be managed in the Biostatistics and Epidemiology unit at Gustave Roussy. Standard institutional practices will be followed to maintain the confidentiality and security of data collected in this study. A copy of the consent form and documentation of consent will be stored in a locked cabinet or an encrypted, password-protected computer drive. All protected health information collected from the study eCRF will be encrypted and password-protected. Questionnaires filled out on paper are stored in a locked cabinet in a secured office in Gustave Roussy. Data will be stored until data analysis is complete and then the data is transferred to a centralized repository. Access to the repository will be limited to the principal investigator, co-investigators, and associates from the original study team. Future studies requesting the use of the data must either be related to the original research study or will require separate IRB approval. The data collected through the eCRF are the data source for the analysis. In order to guarantee the authenticity and the credibility of the data in conformity with good clinical practices, auditing and quality assurance systems include (1) study management in accordance with standardized procedures at Gustave Roussy, (2) quality control performed by the CRA, and (3) auditing of investigating centers. Particularly, it is the responsibility of the CRA (i) to check that the investigator’s file is correctly and regularly updated; (ii) to verify the signatures and validity of consent forms, fulfillment of eligibility criteria, validity of evaluation criteria, and adverse events; and to (iii) assure that reporting requirements are met. Regular meetings (at least monthly) with the investigator from the coordinating center and from other participating centers and study coordinator assure review of study procedures, periodic updates on study progress (including number of patients enrolled on-study as compared to expected numbers), and troubleshoot procedural problems.

### Statistical considerations

Previous meta-analyses indicated that exercise was more effective than control in reducing CRF, with a standardized effect size ~ 0.40 [31, 65–67], but there are limited data on the effect of lifestyle interventions aimed at weight loss on CRF among overweight or obese patients. To detect an effect size of 0.40, a sample size of 101 evaluable patients per arm will provide 80.0% power using a two-sided α = 0.05, two-sample test. The primary test statistic for inference is the time-by-treatment interaction effect in a linear mixed model. This effect size (0.40) is considered as small to moderate by Cohen [68]. Taking some potential drop-out into account, the final sample size for this study is inflated to 220 patients. The primary comparison of CRF among intervention assignments will be performed in the intent-to-treat population of all randomized patients (i.e., all analyses will retain each participant in the group he was randomly assigned regardless of missing data or drop-out status).

The primary analysis of MEDEA will compare the primary endpoint of CRF scores at the M12 post-randomization time point between arms. This comparison between arms will employ a linear mixed model with random patient effect using time as a categorical variable, treatment arm, and a treatment by time interaction with patient-reported CRF measured by appropriate EORTC QLQ-C30 subscale scores. In a sensitivity analysis, baseline characteristics will be added as fixed covariates to the model.

All other measures/time points/analyses will be considered secondary or exploratory analyses. Similar analyses as those specified for the primary endpoint will be performed for other scales. For binary endpoints, chi-squared tests will be used. Further analyses will include analyses of continuous endpoints using mixed-effects models and binary endpoints using generalized estimating equations. The analyses of objectives including IDFS as an endpoint are performed in an intention-to-treat manner.

For the primary analysis of MEDEA (primary endpoint of global CRF), two-sided *p*-values < 0.05 will be considered statistically significant. All other endpoints are considered secondary or exploratory, with no *p*-value adjustment for multiple testing. For interpreting the clinical significance of effects, 0.2, 0.5, and 0.8 standard deviation effects will be considered as small, moderate, and large, respectively [68].

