#### Exploratory objectives

MEDEA also has the following exploratory objectives: exploratory objective 1—assess the impact of the weight loss intervention on cancer-related outcomes (IDFS and overall survival [OS]); exploratory objective 2—assess the adherence to intervention by qualitative and quantitative evaluation. For the qualitative assessment, focus groups will be performed with selected study participants to understand barriers and facilitators to uptake and adherence to the intervention, including satisfaction and suggestions for improvement regarding the weight loss program. Focus groups are envisioned at least once halfway through the intervention (month [M] 6) and once at the completion of the intervention (M12). Table 1 summarizes MEDEA Study outcomes.

**Table 1 Tab1:** MEDEA Study outcomes, measures, and assessment

Outcome type	Outcome		Measure	Type of assessment	Schedule of data collection			
					Baseline, M0	M6	M12	M18
**Primary**	**Cancer-related Fatigue**	**Global fatigue**	EORTC QLQ-C30^1^	Self-reported	X	X	X	X
**Secondary**	**Cancer-related Fatigue**	**Fatigue dimensions: physical, emotional, cognitive**	EORTC QLQ-FA12^2^	Self-reported	X	X	X	X
	**Quality of life, anxiety, and depression**	**Other quality of life domains***	EORTC QLQ-C30^1^	Self-reported	X	X	X	X
			EORTC QLQ-B45^3^	Self-reported	X	X	X	X
		**Anxiety/Depression**	HADS^4^	Self-reported	X	X	X	X
	**Health behaviors**	**Dietary habits**	Food questionnaire^5^	Self-reported	X	X	X	X
		**Physical activity**	WHO GPAQ-16^6^	Self-reported	X	X	X	X
		**Intensity of physical activity**	Actigraph Accelerometer^7^	Device-based	X	X	X	X
		**Energy expenditure**	Actigraph Accelerometer^7^	Device-based	X	X	X	X
		**Daily steps**	Actigraph Accelerometer^7^	Device-based	X	X	X	X
	**Weight and body composition**	**Weight**	Clinical visit	Hospital-based	X	X	X	X
		**Body mass index**	Clinical visit	Hospital-based	X	X	X	X
		**Waist and hip circumference**	Clinical visit	Hospital-based	X	X	X	X
	**Cost-effectiveness**	**Length of all-cause hospitalizations**	Direct medical costs	**	Throughout the whole study duration			
		**Drug consumption:** antidepressants, anxiolytics, pain-killers, and anti-inflammatory drugs (name, start date, duration of use)	Direct medical costs	**	Throughout the whole study duration			
		**Sick leave** (number, duration, and reason)	Indirect costs	**	Throughout the whole study duration			
		**Utility/QALY**	EuroQol 5D 3L^8^	Self-reported	X	X	X	X

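### The primary mixed model does not condition on baseline (M0) fatigue, which forgoes precision: about 10 power points at an assumed M0–M12 correlation of 0.5

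*Protocol article*

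**What the plan says.** All references are to the Protocol article.

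- **Primary model.** Statistical considerations specifies a "linear mixed model with random patient effect using time as a categorical variable, treatment arm, and a treatment by time interaction". It says that arms are compared on fatigue at M12, and it names the time-by-treatment interaction as the primary test statistic.
- **Covariates.** They enter only afterwards: "In a sensitivity analysis, baseline characteristics will be added as fixed covariates to the model". The characteristics are not listed.
- **When fatigue is measured.** Table 1 (under Exploratory objectives) schedules the primary instrument at M0, M6, M12 and M18: "EORTC QLQ-C30^1^ Self-reported X X X X". Under Implementation of study procedures, the study nurse "collects the required baseline study measures including baseline objective anthropometric measures. Randomization then occurs". The M0 score is thus a pre-randomisation measurement.
- **Sample size.** "To detect an effect size of 0.40, a sample size of 101 evaluable patients per arm" gives "80.0% power using a two-sided α = 0.05, two-sample test". No correlation between visits is stated.
- **Other outcomes.** "Similar analyses as those specified for the primary endpoint will be performed for other scales".

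**The concern.** With M0 as one of the visits and a free arm effect, the model gives each arm its own mean at every visit, including M0. Randomisation makes the expected M0 means equal, and the model does not use that fact. If M0 is instead not an outcome row, none of the listed terms contains the M0 score. Either way, the primary estimate is not conditioned on baseline fatigue.

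The cost is a wider confidence interval than the collected data allow. If the raw M12 contrast is reported, any chance M0 imbalance also stays in it. The same model carries over to the other scales. Other risk factors and correlates of CRF lists pre-treatment fatigue among the risk factors for persistent fatigue, so some association between earlier and later fatigue is expected, although the article does not quantify it.

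**Working it through.** **Inputs from Statistical considerations:** 101 evaluable patients per arm, standardised effect 0.40, two-sided α = 0.05. **Assumed:** M0–M12 correlation ρ, which the article does not give (0.5 as the working value, 0.3 to 0.7 as the range); equal variance at M0 and M12; complete data; 0.40 in SDs of the M12 score, except where step 5 varies this.

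**1. The plan's own figure.** Two-sample t test with 200 degrees of freedom and noncentrality 0.40 × √(101/2) = 2.843. Power is 80.8% (81.1% by the normal approximation), so the stated 80.0% is reproduced.

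**2. Variance of each estimate, relative to the raw M12 difference.**

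- Raw M12 contrast: 1
- M12-versus-M0 interaction (difference in change): 2(1 − ρ)
- M12 difference conditioned on M0: 1 − ρ²

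A generalised least squares calculation for four visits with a random patient effect (compound symmetry) gives the same three factors. The third comes from the model with a common M0 mean.

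**3. Direction.** 1 − ρ² never exceeds 1. Also 2(1 − ρ) − (1 − ρ²) = (1 − ρ)², which is never negative. Conditioning on M0 is therefore at least as precise as either stated contrast at every ρ, apart from a negligible cost in degrees of freedom.

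**4. Size.** Power with noncentrality 2.843/√(variance factor); gains are taken before rounding.

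| ρ | Raw M12 | Interaction (factor) | Conditioned on M0 (factor) | Gain over raw | Gain over interaction |
|---|---|---|---|---|---|
| 0.3 | 80.8% | 66.7% (1.40) | 84.3% (0.91) | 3.5 | 17.6 |
| 0.4 | 80.8% | 73.3% (1.20) | 87.0% (0.84) | 6.2 | 13.7 |
| 0.5 | 80.8% | 80.8% (1.00) | 90.4% (0.75) | 9.7 | 9.7 |
| 0.6 | 80.8% | 88.5% (0.80) | 94.2% (0.64) | 13.5 | 5.7 |
| 0.7 | 80.8% | 95.5% (0.60) | 97.7% (0.51) | 17.0 | 2.3 |

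At ρ = 0.5 the confidence interval is 1 − √0.75 = 13% narrower, which is worth 101/0.75 ≈ 135 unadjusted patients per arm. With all 110 randomised patients per arm evaluable, the comparison at ρ = 0.5 is 84.3% against 92.9% (normal approximation), a gain of 8.6 points.

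**5. Dependence on the meaning of 0.40.** The article does not say which SD standardises the effect. If it is the SD of change, the interaction has 80.8% power at every ρ, and conditioning on M0 gives 93.9%, 90.4% and 86.6% at ρ = 0.3, 0.5 and 0.7. The gain over the interaction persists, but the interaction no longer falls short of 80%. On that scale it is the raw M12 contrast that would fall below 80% once ρ exceeds about 0.5 (71.6% at 0.6).

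**The case against.** A reader might infer that baseline fatigue is never used, that power is lost, or that the trial is underpowered. The documents do not support any of these.

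- **M0 is used in the named test.** Measured against M0, the interaction subtracts each patient's M0 score. It uses M0 as an unadjusted change score, which gains nothing over the raw contrast at ρ = 0.5. Chance M0 imbalance remains only in the raw M12 contrast. With missing visits, the mixed model also draws somewhat on M0.
- **Nothing promised is lost at ρ = 0.5.** Either contrast has about 81% power against a stated 80.0%. The loss is of an available gain.
- **A shortfall of the interaction is conditional.** It needs ρ below about 0.5 and an effect of 0.40 expressed in SDs of the M12 score. The article states neither.
- **The model is legitimate.** An arm-by-time mixed model with free means is standard and unbiased under randomisation. This is a point about efficiency.
- **Some inputs are inferred.** That M0 is a level of time follows from the interaction test, but the article does not say so outright. The background remark on fatigue concerns the time before treatment, whereas M0 here follows surgery, chemotherapy and radiation, so its support is indirect.

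These objections limit the claim but do not remove it. One might add that an unseen analysis plan could supply the adjustment. However, the article lists the primary model term by term and places baseline characteristics in a sensitivity analysis. Even if M0 fatigue were among them, that analysis would not be the primary one.

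**Conclusion.** The point holds as one of forgone precision. The stated primary model neither adjusts for M0 fatigue nor imposes a common M0 mean, although the score is available before randomisation. That adjustment would be at least as precise does not depend on ρ; the size of the gain does. At an assumed ρ of 0.5 and 101 per arm, power would go from about 81% to about 90%. Across 0.3 to 0.7, with 0.40 in SDs of the M12 score, the gain is about 4 to 17 points over the raw M12 contrast and about 18 down to 2 over the interaction. The validity of the planned test is not in question. It is worth changing because the data are already collected and the gain extends to the secondary scales.

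**What to change.** In Statistical considerations, before unblinded data are seen, name the baseline-adjusted M12 arm difference as the primary estimate, in one of two forms:

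1. Outcomes M6, M12 and M18, with fixed effects for M0 score, M0 score by time, arm, time and arm by time.
2. M0 kept as an outcome, one M0 mean common to both arms, and an unstructured covariance across visits.

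The two agree closely only with such a covariance. Under the random patient effect now specified, the second form would adjust M12 through a single common correlation, whereas the first estimates a slope at each visit. The results can differ if correlations vary between visits.

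Use the same form for the other continuous scales measured before randomisation. Exclude the accelerometer outcomes: Implementation of study procedures has the devices for the M0 assessment sent out after randomisation.

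**Cost.** No new data, patients or visits are needed. Trial status and data availability reports accrual complete in 2021, so this is a late change to the primary analysis and needs a dated, documented justification. The first form also needs a rule for missing M0 scores; the second does not.

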### Study design

MEDEA is a RCT evaluating the effect of health education alone vs. weight loss intervention plus health education on CRF in overweight and obese women with early-stage breast cancer. Patients are offered to participate in this study during routine consultations. Participants are randomized to a standard health education program (arm 1 control) vs. a 1-year personalized telephone-based health education weight loss follow-up (arm 2 interventional). A permuted block randomization is applied in a 1:1 randomization ratio using a block size of 4. Stratification occurs on the basis of BMI at diagnosis (overweight [BMI 25.0–29.9 kg/m^2^] vs. obese [BMI ≥ 30.0 kg/m^2^]), age (≤ 50 vs. > 50 years), and receipt of endocrine therapy (yes vs. no) (Fig. 1).

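### The primary mixed model names only a random patient effect; on the usual reading this makes the M0-to-M12 interaction test modestly anti-conservative if correlation falls with time between visits

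*Protocol article*

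**What the plan says.** Under Statistical considerations, the protocol article describes the primary model as a "linear mixed model with random patient effect using time as a categorical variable", together with arm and the arm-by-time interaction. The same section states: "The primary test statistic for inference is the time-by-treatment interaction effect in a linear mixed model". It also describes the primary analysis as a comparison of fatigue scores between arms at M12.

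No random slope, residual correlation structure, visit-specific variance or robust standard error is named. The one sensitivity analysis mentioned adds baseline characteristics as fixed covariates and leaves the covariance as it is. Analyses of the other scales are to follow the same pattern.

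Table 1, under "Schedule of data collection", places the fatigue questionnaire at M0, M6, M12 and M18. The text does not say which of these visits enter the primary model.

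**The concern.** A random patient effect with independent, equal-variance residuals implies one common variance and one common correlation for every pair of visits. Repeated symptom scores often behave differently, with visits close together correlating more strongly than visits far apart.

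The M0-to-M12 interaction contrast depends on one correlation only, that between M0 and M12. The fitted model replaces it with an average over all pairs of visits, and 6-month pairs dominate that average. If the average exceeds the true 12-month correlation, the model believes the change from M0 to M12 is less variable than it is. The standard error and p-value are then too small. The trial's conclusion rests on one two-sided test at 0.05, and the same model is carried to the secondary scales without multiplicity adjustment, so a cheap safeguard is worthwhile.

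**Working it through.** **1. The plan's own figure.** The inputs are in Statistical considerations: "To detect an effect size of 0.40", "using a two-sided α = 0.05, two-sample test" and "a sample size of 101 evaluable patients per arm will provide 80.0% power". Allocation is 1:1 (Study design). The normal approximation gives n per arm = 2 × (1.960 + 0.842)² / 0.40² = 98.1, so 99. The t-test solution is 99.08, so 100. At 101 per arm the power is 0.811 (normal) or 0.808 (t-test). The stated size reproduces, and the covariance question does not touch it. Going from 202 to 220 patients allows for 18/220 = 8.2% drop-out.

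**2. Formulas.** Let r6, r12 and r18 be the correlations at gaps of 6, 12 and 18 months, with equal variances (SD = 1), complete data and n patients per arm.

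- True variance of the M0-to-M12 interaction contrast: 2(1 − r12) × 2/n.
- Variance under compound symmetry: 2(1 − r̄) × 2/n. Four visits give three 6-month pairs, two 12-month pairs and one 18-month pair, so r̄ = (3·r6 + 2·r12 + r18)/6.
- SE ratio (model/true) = √[(1 − r̄)/(1 − r12)].
- Actual two-sided error = 2Φ(−1.96 × ratio).

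The model SE is too small when r̄ > r12, that is, when 3(r6 − r12) > r12 − r18. Linear and exponential decay both satisfy this.

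**3. Worked example.** Take exponential decay of 0.7 per 6 months, so 0.70/0.49/0.343. Then r̄ = (2.10 + 0.98 + 0.343)/6 = 0.571. The ratio is √(0.4295/0.51) = 0.918. At n = 101 the model SE is 0.1304 against a true 0.1421. The error is 2Φ(−1.80) = 7.2%.

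**4. Range.** All correlations below are assumptions; the article gives none.

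| r6 / r12 / r18 | r̄ | SE ratio | Actual error |
|---|---|---|---|
| 0.50 / 0.50 / 0.50 | 0.500 | 1.000 | 5.0% |
| 0.60 / 0.55 / 0.50 | 0.567 | 0.981 | 5.4% |
| 0.60 / 0.50 / 0.40 | 0.533 | 0.966 | 5.8% |
| 0.70 / 0.60 / 0.50 | 0.633 | 0.957 | 6.1% |
| 0.50 / 0.25 / 0.125 | 0.354 | 0.928 | 6.9% |
| 0.70 / 0.49 / 0.343 | 0.571 | 0.918 | 7.2% |
| 0.90 / 0.81 / 0.729 | 0.842 | 0.913 | 7.3% |
| 0.60 / 0.58 / 0.40 (late drop) | 0.560 | 1.024 | 4.5% |

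**5. Simulation with drop-out.** The random-intercept model was fitted by REML with 110 per arm, 3% drop-out per visit and 4,000 runs (Monte Carlo error about √(0.05 × 0.95/4000) = 0.3 percentage points). Constant 0.6: SE ratio 1.005, error 4.6%. Linear 0.60/0.50/0.40: 0.971, 5.4%. Exponential 0.7: 0.924, 6.9%. This agrees with the formulas.

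**6. Other readings of the test.**

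- Plain M12 difference between arms: the model variance is the average visit variance × 2/n. With equal variances and complete data the ratio is 1.000 whatever the decay.
- Joint 3-df interaction test over all visits: about 5.1% to 6.8% under typical decay.
- M18 left out of the model: r̄ = (2·r6 + r12)/3. Linear 0.60/0.50 then gives a ratio of 0.931 and 6.8%; exponential 0.7 gives 0.852 and 9.5%.

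**7. Unequal variances at constant correlation 0.5 (assumed).** Let the SDs rise as 1/1.1/1.2/1.2. The true contrast variance factor is 1 + 1.44 − 2(0.5)(1.2) = 1.24. The model uses 2 × (1.2725 − 0.6317) = 1.282, where 1.2725 is the mean variance and 0.6317 the mean covariance. The ratio is √(1.282/1.24) = 1.017, so the test is slightly conservative. With the SDs falling from 1.2 to 1 (1.2/1.1/1/1) the ratio is 0.972. For the plain M12 difference the same two patterns give √(1.2725/1.44) = 0.940 and √(1.1625/1) = 1.078.

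**The case against.** The strongest counter-argument is that compound symmetry follows from what the article leaves unsaid. It names a random patient effect but does not state that residuals are independent or of equal variance, and it does not rule out robust standard errors. An unseen analysis plan could supply either. This stands as a limit on certainty, but it does not remove the point. The article does commit to a dependence structure, its ordinary meaning is a random intercept, and a better choice for four fixed visits is readily available.

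Second, the section describes two different tests. If the p-value comes from the plain M12 difference, decaying correlation does no harm with complete data and equal variances; only unequal variances matter. This also stands. The concern attaches to the interaction, which is the test statistic the section names, and there to the M0-to-M12 contrast.

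Third, size and direction rest on assumed correlations. Constant correlation gives no error, and a drop concentrated after M12 or rising variances can turn the interaction test conservative. That is correct, and the effect is modest in any case.

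A reader might infer that the primary p-value is certain to be wrong, or that the trial is underpowered because of this. The documents support neither: they report no correlations or visit-specific variances, and the stated 101 per arm reproduces.

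**Conclusion.** The point holds in conditional form. It needs three conditions:

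- the random patient effect is fitted with independent, equal-variance residuals;
- the primary test is the M0-to-M12 interaction contrast, with all four visits in the model;
- correlation falls with the gap in a typical way.

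The standard error is then about 2% to 9% too small, and the nominal 5% two-sided error is about 5.4% to 7.3%. Leaving M18 out would raise this further. If any of the three conditions fails, the bias may be absent or may run in the conservative direction. The reading that the primary analysis is invalid as written goes beyond the text. What the text supports is a needlessly restrictive covariance choice with a modest and avoidable risk to the type I error.

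**What to change.** Replace the random patient effect with an unstructured within-patient covariance over the scheduled visits, and state a fallback (for example heterogeneous Toeplitz) if the model does not converge. Alternatively, keep the random patient effect and use robust standard errors. State which visits enter the model, name the M12 contrast that yields the primary p-value, and use the same specification for the other scales.

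The cost is a few sentences in the analysis plan, best settled before the primary comparison is run. Four visits need at most 4 variances + 6 covariances = 10 parameters, which 220 patients can support. Confidence intervals may be slightly wider. Kenward-Roger degrees of freedom are optional at this sample size, and the planned number of patients does not change.

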### Eligibility

#### Inclusion criteria

Patients are eligible if they have histologically confirmed stage I–III breast cancer without evidence of distant metastatic or locally recurrent disease at inclusion. Participants with a history of invasive breast cancer in the 5 years prior to study registration other than the current diagnosis are ineligible for enrollment. Prior ductal carcinoma in situ (DCIS) at any time does not make a patient ineligible. Subjects must have a BMI ≥ 25 kg/m^2^, either objectively assessed at the time of eligibility evaluation or reported in the medical records within 56 days prior to study registration. All adjuvant or neoadjuvant chemotherapy, radiation, and surgery must have been completed no more than 12 months before enrollment. Patients may have breast reconstruction during protocol participation, but definitive breast cancer surgery must be completed prior to registration. Biologic therapy, hormonal therapy, and bisphosphonates are acceptable to be ongoing while on study. Participants should have an ECOG Performance Status of ≤ 1 and self-reported ability to walk at least 400 meters (at any pace). Each participant should understand, sign, and date the written informed consent form prior to any protocol-specific procedures and be able and willing to comply with the study visits and procedures as per protocol. Patients must be able to read and speak French to be eligible for inclusion.

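### The primary model leaves out the three stratification factors: the M12 comparison loses a little precision or, if the interaction is the test, the covariate sensitivity analysis shows almost nothing

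*Protocol article*

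**What the plan says.** All references are to the protocol article.

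- **Study design.** Allocation: "A permuted block randomization is applied in a 1:1 randomization ratio using a block size of 4". On the strata, the section then says: "Stratification occurs on the basis of BMI at diagnosis", with two levels only (25.0–29.9 and 30.0 or more kg/m²). Age (cut at 50 years) and endocrine therapy (yes or no) are the other two factors. That makes 2 × 2 × 2 = 8 strata.
- **Statistical considerations, model.** The primary comparison uses a "linear mixed model with random patient effect using time as a categorical variable, treatment arm, and a treatment by time interaction". None of the three stratification factors is listed.
- **Statistical considerations, contrast.** The section describes the primary inference in two ways. One sentence reads: "The primary test statistic for inference is the time-by-treatment interaction effect in a linear mixed model". The next paragraph says that the primary analysis compares fatigue scores between arms at M12.
- **Statistical considerations, covariates.** "In a sensitivity analysis, baseline characteristics will be added as fixed covariates to the model". The characteristics are not named, and nothing is said about time interactions.
- **Inclusion criteria.** BMI of at least 25 kg/m² is "either objectively assessed at the time of eligibility evaluation or reported in the medical records within 56 days prior to study registration".
- **Table 1.** Fatigue on the QLQ-C30 is collected at M0, M6, M12 and M18.

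**The concern.** Stratified blocks force the arms to be similar on the three factors. If those factors predict fatigue, the between-arm difference varies less than an analysis that ignores them assumes. The background section itself presents BMI as a risk factor for fatigue. The unadjusted M12 test is then conservative, and precision that the design has already secured is not used.

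The planned covariate analysis might seem to make up for this. Whether it does depends on the contrast. A covariate that is constant over time and entered as a main effect shifts all of a patient's scores equally, so it drops out of a change from M0. If the interaction is the test, agreement between the primary and sensitivity results is largely built in and could be mistaken for robustness.

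Separately, enrolment can be up to 12 months after the end of surgery, chemotherapy and radiation, and the background notes weight gain following treatment. A patient could be below 25 kg/m² at diagnosis and eligible at enrolment, yet fit neither BMI level as written.

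**Working it through.** **1. The plan's own figure.** Inputs: standardised effect d = 0.40, two-sided α = 0.05, power 80.0%, 101 evaluable per arm. The normal approximation gives 99 per arm and the t-test 99.08, so 100. At 101 per arm, power is Φ(0.40 × √(101/2) − 1.96) = Φ(2.843 − 1.960) = 81.1% (t-test 80.8%). The stated figure reproduces. The inflation from 202 to 220 implies drop-out of 18/220 = 8.2%.

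**2. M12 between-arm difference.** Let R² be the share of M12 variance explained by the stratification factors. The article gives no value, so a range is shown. With near-perfect balance on the factors:

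- unadjusted SE relative to adjusted SE: 1/√(1 − R²)
- actual type I error of the unadjusted test: 2 × [1 − Φ(1.96/√(1 − R²))]
- adjusted power: Φ(2.843/√(1 − R²) − 1.96)

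| R² (assumed) | SE ratio | Actual type I error, unadjusted | Power, adjusted |
|---|---|---|---|
| 0 | 1.000 | 0.050 | 81.1% |
| 0.02 | 1.010 | 0.048 | 81.9% |
| 0.05 | 1.026 | 0.044 | 83.1% |
| 0.10 | 1.054 | 0.039 | 85.0% |

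Balance is not quite perfect. With blocks of 4, an incomplete block leaves a stratum unequal by at most 2 patients.

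**3. Time-by-treatment interaction at M12.** Write the score of patient i at visit t as time, arm and arm-by-time terms + βxᵢ + uᵢ + eᵢₜ, where xᵢ is a baseline covariate and uᵢ the patient effect. In the change from M0 to M12, both βxᵢ and uᵢ cancel. With complete data, the interaction estimate is the between-arm difference in mean change. Its standard error depends only on the within-patient variance, so adding xᵢ as a main effect leaves both unchanged.

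**4. Simulation of the stated model.** Settings, all assumed: 220 patients, four visits, stratified blocks of 4, the three factors explaining 10% of total variance, intraclass correlation about 0.55. The random-intercept model was fitted with and without main effects of the factors, in 60 runs per drop-out rate.

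| Drop-out per visit | Interaction: largest change in estimate (SD) | Interaction: mean SE ratio | Interaction: largest change in z | M12 difference: mean SE ratio | M12 difference: largest change in z |
|---|---|---|---|---|---|
| 0 | 0.000 | 1.000 | 0.00 | 0.950 | 0.45 |
| 2.8% (about 8% by M18) | 0.011 | 0.9995 | 0.08 | 0.951 | 0.42 |
| 10% | 0.023 | 0.998 | 0.16 | 0.955 | 0.35 |

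These are maxima over 60 runs, not bounds. One further data set at 10% drop-out per visit showed an interaction shift of 0.22 (z from −2.52 to −2.73).

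**5. By-visit coefficients.** Factor-by-time terms can change the interaction test even with complete data. In one complete data set, z went from −5.106 to −5.074. In the same data set, the SE of the M12 difference was 0.1328 unadjusted, 0.1199 with main effects and 0.1201 with by-visit terms, so the extra terms cost almost no precision.

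**6. BMI timing.** Study design allows two BMI levels, both starting at 25.0 kg/m² and dated at diagnosis. Inclusion criteria date the same threshold at eligibility evaluation or within 56 days before registration. Nothing in the article requires BMI of at least 25 at diagnosis.

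**The case against.** **The two harms cannot be added together.** If the interaction is the test, leaving out main effects costs it essentially nothing, and the figures in step 2 do not apply. If the M12 difference is the test, the sensitivity analysis is informative: it cuts the SE by about 5% at R² = 0.10. This objection stands in full, so the point has to be put as two alternatives.

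**A reader might infer that the sensitivity analysis can never change the interaction result.** That is exact only with complete data, main effects alone and M0 among the outcomes. The article expects drop-out and does not exclude covariate-by-time terms. Nearly uninformative is as far as the text goes.

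**A reader might infer that the primary result is biased or its error rate inflated.** It is neither. The unadjusted M12 test errs on the conservative side and still reaches the planned 80% at 101 per arm. R² is assumed, and at 2% the gain is under one percentage point of power.

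**Covariate detail belongs in the analysis plan.** The names and coding of the sensitivity covariates can be left there, and their absence is not criticised here. The primary model's terms, however, are listed in the article, and adjustment is expressly placed in a sensitivity analysis. That is stated text.

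**A reader might infer that some patients were randomised without a stratum.** The coding in the online randomisation module is not shown, and the number of patients concerned is unknown. Only the mismatch in the text is established.

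**Conclusion.** The point holds as a modest, inexpensive improvement and does not threaten validity.

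- **If the M12 difference is tested:** the factors belong in the primary model. Omitting them costs roughly 1 to 4 percentage points of power and brings the actual type I error to about 0.048–0.039, for an assumed R² of 2–10% and near-perfect balance.
- **If the interaction is tested:** the omission is nearly free, but a main-effects sensitivity analysis says little. It changes nothing with complete data. In the 60 runs at about the drop-out implied by the sample size, z shifted by at most 0.08.

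The article supports both readings of the primary contrast, and each leaves something to correct. The BMI definitions disagree on timing. The practical effect of that cannot be sized from the document.

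**What to change.** 1. State that the between-arm difference at M12 is the primary contrast, and include BMI stratum, age group and endocrine therapy in the primary model with by-visit coefficients.
2. In any sensitivity model that keeps M0 as an outcome, enter the covariates with their time interactions.
3. Reconcile the BMI timing in Study design and Inclusion criteria. Check in the randomisation records how any eligible patient with BMI below 25 kg/m² at diagnosis was stratified.
4. Adjust for the BMI factor as actually used in the randomisation. BMI measured at M0 can be added as an optional further covariate, but should not replace it.

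The cost is a change of wording in the analysis plan and one check of existing records. The variables are already collected, and the sample size does not change.
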